#### Genetic

A separate blood sample will be collected pre-randomization for the analysis of single nucleotide polymorphisms (SNP) in the *APOE* and the *MTHFR* genes. The *APOE*-ϵ4 allele has been found to be associated with an increased risk of developing AD as well as cognitive decline in normal elderly [130,131]. Testing for allelic differences in the *APOE* gene was included in the current study in order to determine whether these genetic differences may affect the efficacy of Lacprodan® PL-20 as a treatment for AAMI. MTHR is an important enzyme involved in the metabolism of HCy. The *MTHFR* 677 T allele is associated with reduced enzymatic activity, which results in decreased serum and plasma levels of folate as well as increased plasma levels of HCy [132]. In consideration of the relationship between levels of phospholipids, vitamin B12 and HCy [53,118], genetic testing for allelic differences in the *MTHFR* gene was included in the current study in order to assess whether this may also affect the efficacy of Lacprodan® PL-20 as an AAMI treatment.

#### Neuroimaging

Neuroimaging with fMRI and MEG will be conducted in a subset of 60 participants in order to further explore the *in vivo* mechanisms of action of Lacprodan® PL-20 in the brain. Previous neuroimaging studies using PS supplementation in AD have been conducted using electroencephalography (EEG) as well as positron emission tomography (PET) [133-135]. PET results revealed that for the PS group there was increased glucose metabolism during a visual recognition task across a number of brain regions, most notably the temperoparietal regions [133]. However, to date no further neuroimaging studies have been conducted using phospholipid interventions, and to the best of our knowledge none have been conducted using MRI or MEG.

In the current study structural and functional MRI scans will be acquired using a Siemens 3 Tesla Tim Trio MRI scanner (Erlangen, Germany), located at the Centre for Human Psychopharmacology, Swinburne University of Technology. During the initial scan, a structural image will be obtained for each participant and used as a reference point for further functional scans. Scanning for DTI analysis, a measure of white matter integrity, will also be conducted. Following DTI there will be scanning in a resting state in order to assess activity in the default mode network (DMN) for approximately 6 minutes. Additional analysis of cell membrane fluidity will also be conducted by using the T2 signal timing information (relaxometry) while in a resting state. Changes in the blood oxygenation-level dependent (BOLD) signal will also be analysed while participants complete in-scanner versions of verbal episodic memory (approximately 20 minutes) and N-Back working memory tasks (approximately 20 minutes).

MEG scanning will be conducted using an Elekta Neuromag® TRIUX 306-Channel Magnetometer system (Helsinki, Finland) MEG system, also located at the Centre for Human Psychopharmacology, Swinburne University of Technology. Initial scanning while in a resting state will be conducted in order to collect information as to activity in the DMN. Following this scanning will be conducted whilst participants complete the same in-scanner tasks as used in the fMRI task: verbal episodic memory and N-Back working memory. The two tasks are kept the same across both fMRI and MEG in order for information from the two imaging modalities to be combined into a single comprehensive analysis. MEG scanning provides important complementary information, which is additional to that provided by fMRI. The temporal resolution of MEG is far superior to fMRI; MEG is capable of recording neural oscillations from delta right through to the gamma range (>40 Hz). Although the spatial resolution of MEG is less than that of fMRI, the high number of sensors (approximately 300), together with modern source reconstruction algorithms (for example, beam forming) means that the spatial resolution of MEG is far superior to conventional scalp-recorded EEG [135]. The combination of the two imaging modalities is state-of-the-art and will provide an unparalleled level of analysis of the effects of Lacprodan® PL-20 on memory function.

All primary and secondary outcome measures are displayed in Table 2.

**Table 2 T2:** Summary of PLICAR outcome measures by visit

	**Measures**	**V1**	**V2**	**V3**	**V4**
Screening	Written informed consent	X			
	Demographics	X			
	Medical history	X			
	Inclusion/exclusion criteria	X	X	X	X
	Concomitant medications	X	X	X	X
	Adverse events	X	X	X	X
	Dietary questionnaire	X			
Cognitive	Memory Complaint Questionnaire (MAC-Q)	X			
	Wechsler Memory Scale Revised (WMS-R)	X			
	Raven’s Progressive Matrices (RPM)	X			
	Mini Mental State Exam (MMSE)	X	X	X	X
	Rey Verbal Learning Test (RVLT)	X	X	X	X
	SUCCAB Spatial Working Memory	X	X	X	X
	SUCCAB Contextual Memory	X	X	X	X
	Prospective and Retrospective Memory (PRMQ)	X	X	X	X
	Rapid visual information processing (RVIP)	X	X	X	X
	Serial 3 s and 7 s subtraction	X	X	X	X
	Jensen box task	X	X	X	X
Mood	Beck Depression Inventory (BDI-II)	X			
	Depression, Anxiety and Stress Scale (DASS)	X	X	X	X
	Profile of Mood States (POMS)	X	X	X	X
	Bond-Lader visual analogue mood scales	X	X	X	X
Cardiovascular	Brachial blood pressure		X	X	X
	SphygmoCor (Aortic blood pressure, pulse pressure, PWV)		X	X	X
	Blood velocity (MCA and CCA)		X	X	X
GI microbiota	Intestinal bacteria		X	X	X
Biochemical	Oxidative stress (Glutathione and F2 isoprostanes)		X	X	X
	Inflammation (TNF-α, IL-1β, IL-6 and CRP)		X	X	X
	B Vitamins (B6, B9 and B12)		X	X	X
	Homocysteine (HCy)		X	X	X
	Glucoregulation		X	X	X
	Serum choline		X	X	X
Genetic	Apolipoprotein E and MTHFR		X		
Brain imaging	Structural magnetic resonance imaging (MRI)		X		X
	Diffusion tensor imaging (MRI)		X		X
	Default mode network activation (MEG and MRI)		X		X
	Relaxometry (MRI)		X		X
	Episodic Memory task (functional MRI and MEG)		X		X
	N-Back working memory task (functional MRI and MEG)		X		X

V1, screening/practice session; V2, baseline visit; V3, 9-day visit; V4, 180-day visit; GI, gastrointestinal; SUCCAB, Spatial Working memory and Contextual Memory tasks from the Swinburne University Computerized Cognitive Ageing Battery; PWV, pulse wave velocity; MCA, medial carotid artery; CCA, common carotid artery; CRP, C-reactive protein; MTHFR, Methyltetrahydrofolate reductase; MEG, magnetoencephalography.

### Analysis

The primary analysis will investigate the effect of treatment on all cognitive outcomes from baseline to 180 days, using the groups as randomized (intention to treat). Statistical analyses will be conducted using linear mixed modelling, whereby subject-specific random intercepts and slopes will be fitted to subject data and fixed effects will be fitted to treatment group, time and the treatment × time interaction. On the basis of *APOE* and *MTHFR* genotyping, subgroup analysis will also be conducted in order to investigate the effect of allelic differences on treatment response. Secondary outcome variables will be analysed using similar statistical techniques. Results will be considered statistically significant at an alpha level of *P* <0.05 corrected for multiple comparisons.

Although stratification according to age, intelligence and baseline WMS-R scores may help to explain some of the residual between-group variance unrelated to the treatment effect, further exploration of possible covariates will also be investigated. Baseline correlations between the primary cognitive outcome measures and other baseline variables, including BMI, educational background, diet, CV function, GI microbiota and biochemical parameters, will also be investigated in order to investigate other important covariates. In the event that significant correlations at the *P* <0.05 level are found at baseline then these additional variables will also be controlled for in the primary analysis of cognitive outcomes.

Analysis of functional neuroimaging data (both MEG and fMRI) during episodic memory and N-Back working memory tasks will be conducted using a region of interest (ROI) approach. Using this method, between-group (Lacprodan® PL-20 versus MPC and inert placebo) functional differences in predefined brain regions will be statistically analysed. The ROIs for the episodic memory task will include the medial temporal lobes, the lateral prefrontal cortices, the associative temporal and paretial regions, the cingulate gyrus and the cerebellum. The ROIs that will be analysed in the N-Back working memory task will include the dorsolateral, ventrolateral and medial prefrontal cortex, anterior cingulate, parietal cortex and sensorimotor cortex [136].

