**Methods:**

In order to reduce the effects of age-associated memory impairment (AAMI) the Phospholipid Intervention for Cognitive Ageing Reversal (PLICAR) was developed to test the efficacy of a milk protein concentrate rich in natural, non-synthetic milk phospholipids (Lacprodan® PL-20). PLICAR is a randomized, double-blind, placebo-controlled parallel-groups study where 150 (N = 50/group) AAMI participants aged > 55 years will be randomized to receive a daily supplement of Lacprodan® PL-20 or one of two placebos (phospholipid-free milk protein concentrate or inert rice starch) over a 6-month (180-day) period. Participants will undergo testing at baseline, 90 days and 180 days. The primary outcome is a composite memory score from the Rey Auditory Verbal Learning Test. Secondary outcomes include cognitive (verbal learning, working memory, prospective and retrospective memory, processing speed and attention), mood (depression, anxiety, stress and visual analogue scales), cardiovascular (blood pressure, blood velocity and pulse wave pressure), gastrointestinal microbiota and biochemical measures (oxidative stress, inflammation, B vitamins and Homocysteine, glucoregulation and serum choline). Allelic differences in the Apolipoprotein E and (APOE) and *Methylenetetrahydrofolate reductase* (MTHFR) gene will be included for subgroup analysis. A subset (N = 60; 20/group)) will undergo neuroimaging using functional magnetic resonance imaging (fMRI) and magnetoencephalography (MEG) in order to further explore *in vivo* central mechanisms of action of Lacprodan® PL-20. This study will enable evaluation of the efficacy of milk-derived phospholipids for AAMI, and their mechanisms of action.

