On the basis of previous human clinical studies with bovine and plant-derived phospholipids, it is hypothesised that in comparison to the inert placebo, Lacprodan® PL-20 supplementation over 180 days will result in significant improvements on our primary variable, namely a composite memory score computed from the Rey’s Verbal Learning Test (RVLT). We are also exploring the possibly that the treatment may benefit other elements of cognitive performance (including processing speed and global functioning). A second hypothesis is that cognitive benefits of a lesser magnitude will be observed when comparing supplementation with Lacprodan® PL-20 with milk protein concentrate (MPC) without phospholipids placebo over 180 days. Additionally we are exploring the effects of Lacprodan® PL-20 on a number of central, CV and GI biomarkers.

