### Primary outcomes

The primary study outcome is the effect of Lacprodan® PL-20 supplementation on memory as measured using a compound score from the RVLT [69,70], similar to that used previously [71]. The memory score will be derived using the formula:

$$\begin{array}{l} \left(Z_{15‒\mathrm{Word}\;\mathrm{Learning}\;\mathrm{test}‘\mathrm{total}\;\mathrm{immediate}\;\mathrm{recall}}’\right)\\ \;+Z_{15‒\mathrm{Word}\;\mathrm{Learning}\;\mathrm{Test}‘\mathrm{maximum}\;\mathrm{immediate}\;\mathrm{recall}’}\\ \left(\;+Z_{15‒\mathrm{Word}\;\mathrm{Learning}\;\mathrm{Test}‘\mathrm{delayed}\;\mathrm{recall}’}\right)/3. \end{array}$$

The RVLT is a test of verbal learning and memory that has a long history of use both in the assessment of clinical memory disturbances as well as cognitive decline associated with normal ageing [70]. Verbal learning, as measured by the RVLT and similar tests, has previously been found to be sensitive to the effects of phospholipid interventions in AAMI populations [39,41]. Similarly, verbal memory has also been found to be sensitive to other nutraceutical interventions such as *Bacopa monnieri*[72] and folic acid [71] in elderly populations. For these reasons, the inclusion of the RVLT will enable direct comparison of the efficacy of the milk-derived phospholipids present in Lacprodan® PL-20 to previous cognitive intervention studies in the elderly.

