### Secondary outcomes

A range of secondary outcomes will be used, encompassing cognitive performance, mood, CV, GI microbiota, biochemical, genetic and brain imaging modalities. Secondary outcomes will include other elements of cognitive performance as measured by a battery of well-validated and highly sensitive cognitive tests. Traditional paper-and-pencil neuropsychological tests as well as computerized tasks have been included. These tests will be implemented at baseline, 90 days and 180 days (pre-dose) in order to capture chronic effects. This battery will consist of the MMSE [65], the Prospective and Retrospective Memory Questionnaire (PRMQ) [73], RVLT [69,70], Spatial Working memory and Contextual Memory tasks from the Swinburne University Computerized Cognitive Ageing Battery (SUCCAB [74]), rapid visual information processing (RVIP), serial 3 s and 7 s subtraction and the Hick’s reaction time paradigm. In order to capture potential acute cognitive effects associated with Lacprodan® PL-20 supplementation, the SUCCAB tests, RVIP, serial 3 s and 7 s subtraction and Hick’s reaction time will also be administered 90 minutes post dose.

The MMSE [65] is a global measure of cognitive function that has been used extensively both as a diagnostic tool for dementia screening as well as a cognitive outcome measure for gauging the efficacy of chronic nutraceutical interventions in elderly participants, for example [71,75,76]. The MMSE was included in the current study due to its widespread use in previous research; however problems with ceiling effects and insensitivity to change amongst high-functioning individuals have been previously well-documented [77].

The PRMQ [73] is a self-report instrument which provides a measure of retrospective as well as prospective memory slips in everyday life. The PRMQ was included in the current study in order to provide an ecologically valid measure of typical memory complaints that may be of concern to elderly individuals. Although most memory complaint questionnaires focus exclusively on failures to remember previous information (retrospective memory), the PRMQ is unique in that it additionally provides a measure of prospective memory failures, which are failures relating to tasks that need to be completed at a certain time (for example, remembering to turn up to an appointment on time) [73,78].

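### The Analysis section widens the primary analysis to all cognitive outcomes, contradicting the single RVLT composite on which the trial is defined and sized

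*Protocol article*

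**What the plan says.** One primary outcome is named in three places in the protocol article:

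- Abstract, Methods: "The primary outcome is a composite memory score from the Rey Auditory Verbal Learning Test".
- Aims and study hypotheses: "our primary variable, namely a composite memory score computed from the Rey’s Verbal Learning Test (RVLT").
- Primary outcomes: "The primary study outcome is the effect of Lacprodan® PL-20 supplementation on memory as measured using a compound score from the RVLT". A formula follows, the mean of three RVLT z-scores.

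The Sample size section attaches f = 0.14 and 80% power to that variable, with alpha 0.05 and no adjustment.

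The rest of cognition has a lower rank. The hypotheses section says "We are also exploring the possibly that the treatment may benefit other elements of cognitive performance", and the Secondary outcomes section says "Secondary outcomes will include other elements of cognitive performance as measured by a battery of well-validated and highly sensitive cognitive tests".

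The Analysis section departs from this. It opens with "The primary analysis will investigate the effect of treatment on all cognitive outcomes from baseline to 180 days". Its next paragraph, on choosing covariates, uses a plural: "Baseline correlations between the primary cognitive outcome measures and other baseline variables". Secondary outcome variables have a separate sentence. One significance rule covers everything: "Results will be considered statistically significant at an alpha level of *P* <0.05 corrected for multiple comparisons".

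**The concern.** The two descriptions cannot both be followed. Under the Primary outcomes section, one composite carries the confirmatory claim. Under the Analysis section as written, tests that the article elsewhere calls secondary belong to the primary analysis. An analysis plan built on either could claim to match the protocol.

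The correction rule makes this more than a matter of wording. It applies to results in general and does not exempt the RVLT composite, whereas the sample size calculation gives that composite the whole 0.05. Depending on the scope of the correction, either several results labelled primary could be tested at 0.05 each, or the RVLT composite would share its alpha with tests for which the trial was not sized.

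**Working it through.** **Inputs.** From the Sample size section: f = 0.14, alpha = 0.05, r = 0.5, three groups, 150 randomized, 20% drop-out, treatment × time interaction from baseline to 180 days, stated power 80%. From Table 2: eight cognitive rows measured at V2 to V4, namely MMSE, RVLT, SUCCAB spatial working memory, SUCCAB contextual memory, PRMQ, RVIP, serial subtraction and the Jensen box task. MAC-Q, WMS-R and RPM are recorded at V1 only and are not counted. Eight is a lower bound, because serial 3s and 7s or subscores could be counted separately.

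**Formula.** Repeated-measures within–between interaction, sphericity assumed, with k groups and m occasions: λ = f²·N·m/(1 − r), df1 = (k − 1)(m − 1), df2 = (N − k)(m − 1). Power is taken from the noncentral F distribution.

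**Reproducing the plan's figure.** With m = 2:

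- N = 125 (150/1.2): λ = 0.0196 × 125 × 2/0.5 = 9.80, df 2 and 122, power 79.7%. This reproduces the stated 80%.
- N = 120 (150 × 0.8): λ = 9.41, df 2 and 117, power 77.9%, slightly under the stated figure.

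With m = 3 and N = 120: λ = 14.11, df 4 and 234, power 86.2%.

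**Case A: the correction does not span the cognitive outcomes.** Eight tests at 0.05 each.

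- Independent tests: 1 − 0.95⁸ = 33.7%.
- Equally correlated tests, by simulation with normal test statistics: about 30%, 25% and 19% at correlations of 0.3, 0.5 and 0.7. Using the two-degree-of-freedom statistic of a three-arm comparison moves each of these by less than one percentage point.

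The correlations are assumptions; the article gives none.

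**Case B: the correction spans them.** As an example, Bonferroni over eight: 0.05/8 = 0.00625.

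| N | Occasions | Power at 0.05 | Power at 0.00625 |
|---|---|---|---|
| 125 | 2 | 79.7% | 51.7% |
| 120 | 2 | 77.9% | 49.2% |
| 120 | 3 | 86.2% | 62.4% |

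Counting 7 to 10 outcomes instead of eight gives corrected power of 46–53% with two occasions, and uncorrected family-wise error of 30–40% under independence. Restoring 80% power at 0.00625 with two occasions needs about 198 completers, which is 198/0.8 = 248 randomized, against the planned 150.

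**The case against.** The best defence is that the primary outcome is fixed repeatedly and precisely outside the Analysis section, and that this section speaks of a primary analysis, not of new primary outcomes. On that view the sentence only describes the main intention-to-treat model for cognition, as distinct from the genotype, biomarker and imaging analyses. This reading is possible, and it tells against inferring that any of the eight tests could legitimately carry the trial's main claim: the definition, the hypothesis and the sample size all point to the RVLT composite. It does not remove the conflict, because the section repeats the plural when choosing covariates and gives secondary variables a sentence of their own.

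The second defence is that a correction is stated, and that its method and family may properly be left to an analysis plan that is not shown. That also stands. A reader might infer that the error rate is simply uncontrolled. The text does not support this, since inflation arises only if the correction leaves out the cognitive outcomes. A reader might equally infer that correction removes the power of the primary outcome. The text does not say that the RVLT composite shares alpha with seven others, and it does not name Bonferroni. The correction might concern the three arms or only the secondary outcomes. Holm or an ordered procedure would cost less than the figures in Case B.

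What cannot be left to an analysis plan is which outcome is primary, because this document already answers that in two incompatible ways.

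**Conclusion.** The point holds as a contradiction in the current text over the scope of the primary analysis. The absence of a named correction method is not itself the fault.

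The numerical consequences are conditional. If the correction does not cover the cognitive outcomes, family-wise error is about 19–34%, given eight tests and assumed correlations between 0.7 and 0. If it covers them by single-step Bonferroni over eight, RVLT power is about 49–52% with two occasions, or 62% with three occasions and 120 completers. These power figures rest on the plan's own f and r. They represent a serious loss from the planned level, not a complete loss of power. If the RVLT composite is the sole primary outcome at 0.05, neither consequence arises and the planned power stands at 79.7% (N = 125) or 77.9% (N = 120) with two occasions.

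**What to change.** In the Analysis section:

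1. State that the primary analysis is the treatment × time effect on the pre-dose RVLT composite from baseline to 180 days, tested at the alpha of 0.05 used in the Sample size section and not shared with other cognitive outcomes. Pre-dose should be written out because the Visit 2 section describes post-dose testing on every cognitive measure, whereas the Secondary outcomes section leaves the RVLT out of the post-dose set.
2. In the covariate paragraph, replace the plural primary measures with the single primary outcome.
3. Move the other cognitive outcomes to the secondary analysis and apply the multiplicity correction within that family, for example by Holm or a false discovery rate procedure.

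This wording does not settle how the comparisons with the two control arms are handled once the overall interaction has been tested; that needs its own statement. The cost is a few sentences and no extra data or participants. The article reports that the trial is still recruiting, so the change can be made before the treatment code is opened.

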#### Visit 2 (Baseline)

The second visit will be scheduled for one week following the screening/practice visit. In preparation for the baseline visit, all participants will be required to collect and store their faecal sample (as per the procedure provided in the faecal sample collection kit) a day before the actual visit. The faecal sample for GI microbiota analysis will be deposited at the Centre for Human Psychopharmacology, Swinburne University, when the participant comes for the baseline visit. The faecal samples will be stored at -80°C until further analysis. Also in preparation, participants will be required to fast from 10 pm the night before. A fasting blood sample will then be taken in order to assess the baseline biochemical measures, together with a separate blood sample, which will be used for Apolipoprotein E (APOE) and *Methylenetetrahydrofolate reductas*e (*MTHFR*) genotyping. Following the blood samples, participants will eat a light breakfast. Half an hour after breakfast, participants will be required to complete all pre-dose cognitive, mood and CV measures. Participants will then be randomized to their treatment group (Lacprodan PL-20® or MPC or rice starch) and consume their first sachet of study treatment dissolved in water. A lunch break of 90 minutes will then follow, before post dose testing on all cognitive, mood and cardiovascular measures. At the conclusion of the baseline study visit, participants will be provided with enough study treatment for the next 90 days.

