### Sample size

Based on the reviewed literature, we predict a small-medium effect size (*f* = 0.14) on the primary variable. The sample size for this study is 150 participants, with 50 participants in each treatment group (Lacprodan® PL-20, MPC or rice starch). Allowing for a 20% drop-out rate over the course of the 180-day testing period, this will give 80% power to detect significant treatment × time interactions from baseline to 180 days for the primary outcome (calculated using G*Power 3.1, with α = 0.05 and *r* = 0.5 for the correlation between repeated measures).

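### The primary mixed model estimates a separate baseline mean for each arm and so tests raw change; a common baseline mean would gain precision at no cost (25% less variance under the plan's own r = 0.5 and equal variances)

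*Protocol article*

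**What the plan says.** The Analysis section fits a linear mixed model by intention to treat to data from baseline to 180 days. For the random part, "subject-specific random intercepts and slopes will be fitted to subject data". For the fixed part, "fixed effects will be fitted to treatment group, time and the treatment × time interaction". Nothing in the section ties the arms to one baseline mean or uses the baseline RVLT composite as a covariate. The covariates it does consider are other baseline variables (body mass index, education, diet and so on), kept if they correlate with the cognitive outcomes at baseline.

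Under Visit 2 (Baseline), the pre-dose cognitive battery comes first; then "Participants will then be randomized to their treatment group". Table 2 lists the RVLT at that visit. Stratification (Methods/Design) uses age, Raven's matrices and the baseline Wechsler memory score, not the RVLT.

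The Sample size section claims "80% power to detect significant treatment × time interactions from baseline to 180 days for the primary outcome", with "α = 0.05 and *r* = 0.5 for the correlation between repeated measures". It assumes f = 0.14, 50 per arm and 20% drop-out.

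**The concern.** A group main effect in a model that has baseline among the responses gives each arm its own free baseline mean. The treatment × time term then measures each arm's departure from its own observed baseline, which is a comparison of raw change. Because the RVLT is measured before allocation, any baseline difference between arms is chance. A model that uses this fact removes part of the noise in the day-180 comparison and corrects for chance imbalance in the baseline score.

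The covariates already planned do not do this. Covariates added only as main effects, while baseline stays in the response, leave the treatment × time contrast essentially unchanged. At stake is precision on the primary outcome, from a measurement the trial already collects.

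**Working it through.** **Inputs from the protocol article.** Three arms, 50 each, 20% drop-out, f = 0.14, α = 0.05, r = 0.5 (Sample size); free group, time and interaction effects with random intercepts and slopes (Analysis); RVLT before randomisation (Visit 2, Table 2).

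**1. The plan's own figure.** For the within-between interaction in G*Power, λ = f²·N·m/(1 − r), df1 = (g − 1)(m − 1), df2 = (N − g)(m − 1). With g = 3 arms and m = 2 times (baseline, 180 days), 80% power needs N = 126.
- 126 × 1.2 = 151.2, close to the stated 150; 126/0.8 = 157.5 is not. The stated size is reproduced if drop-out was added as a multiplier.
- With 20% lost from 150, N = 120 and λ = 0.0196 × 120 × 2/0.5 = 9.41, giving 77.9% power.

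**2. Variance of the day-180 contrast, equal variances.** In units of the single-visit SD², per subject:
- free baseline means (raw change): 2(1 − r) = 1.00 at r = 0.5
- common baseline mean: 1 − r² = 0.75
- ratio: (1 − r²)/[2(1 − r)] = (1 + r)/2 = 0.75

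Information matrices for the two mixed models, 40 per arm, agree:

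| Visits and time coding | Free | Common | Ratio |
|---|---|---|---|
| 2 visits | 0.0500 | 0.0375 | 0.750 |
| 3 visits, categorical | 0.0500 | 0.0375 | 0.750 |
| 3 visits, linear | 0.0500 | 0.0364 | 0.727 |

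The standard error falls from 0.2236 to 0.1936 SD. For other r, the ratio is 0.65 at 0.3, 0.80 at 0.6, 0.85 at 0.7 and 0.90 at 0.8.

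**3. Power of the planned F test.** Dividing λ by 0.75 gives 12.54. At 120 completers, power goes from 77.9% to 88.9%. Completers needed for 80% fall from 126 to 96.

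**4. Unequal variances.** Let V₀ and V₁ be the baseline and day-180 variances, C their covariance and β = C/V₀. Raw-change variance minus adjusted variance is (V₀ + V₁ − 2C) − (V₁ − C²/V₀) = V₀(1 − β)². This is never negative, and it is zero when β = 1. The random-effect variances below are assumed for illustration, with time scaled so that 180 days = 1; the ratio uses categorical time.

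| Intercept, slope, covariance, residual | r (0–180) | β | Ratio |
|---|---|---|---|
| 0.6, 0.5, −0.1, 0.4 | 0.44 | 0.50 | 0.81 |
| 0.5, 0.3, 0.05, 0.5 | 0.47 | 0.55 | 0.84 |
| 0.6, 0.2, 0, 0.4 | 0.55 | 0.60 | 0.84 |
| 0.7, 0.3, 0, 0.3 | 0.61 | 0.70 | 0.90 |
| 0.5, 0.3, 0.2, 0.5 | 0.54 | 0.70 | 0.93 |
| 0.7, 0.5, 0.3, 0.3 | 0.69 | 1.00 | 1.00 |

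With linear time, the first row is 0.79. Apart from the last row, the gain is therefore about 7% to 21%.

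**5. Pairwise comparisons.** The document gives no pairwise effect, so one must be assumed. At 40 per arm, f = 0.14 fixes the sum of squared arm deviations at 9.408/40 = 0.2352. The powers below use the pooled 117 residual degrees of freedom.
- Both comparators change identically: 2d²/3 = 0.2352, so d = 0.594 SD. Power goes from 75% to 86% at α = 0.05.
- Milk protein concentrate (MPC) midway between the other two arms: d²/2 = 0.2352, so d = 0.686 SD against rice starch. Power goes from 86% to 94%.

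**The case against.** The planned model is standard and unbiased under randomisation. The sample size is computed for the same interaction, so design and analysis agree, and the stated power already pays for the change-score variance. That stands. A reader might infer that the primary analysis is biased or invalid; nothing in the document supports this.

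The 25% belongs to the planning assumptions. The planned random slopes let variance change over time, and then the gain can be small or nil. A reader might infer that adjustment helps whenever the correlation is below 1. The last row of the second table refutes this, with r = 0.69 and no gain.

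Nor does the document show a serious power shortfall. The planned test is about two points short at 120 completers with two times, and has 86.2% power if three times enter the calculation. The pairwise figures depend on where MPC lies. The second hypothesis expects a lesser benefit against MPC, so identical change in both comparators is not the obvious case.

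Stratification on a related memory score may already limit chance imbalance in the RVLT. How far depends on a correlation the article does not give.

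The article condenses a fuller plan, and how baseline enters a model is often settled there. But this article states the fixed effects explicitly, so the comment is on a model it specifies.

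**Conclusion.** The point holds as a free improvement. The stated model treats baseline as an outcome with a free mean in each arm, and its day-180 interaction is the raw-change contrast (exactly so with complete data). The loss is of precision only.

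The headline size, a 25% cut in variance and power from about 78% to 89%, rests on r = 0.5, equal variances at baseline and day 180, two time points and 120 completers. Under equal variances the cut is 35% at r = 0.3 and 15% at r = 0.7. Where variance grows over time, expect less, down to nothing when β = 1. The constrained model is not expected to be less precise than the planned one in any of these cases.

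**What to change.** State the primary model as follows: the RVLT composite at baseline, day 90 and day 180 are all responses; the three arms share one baseline mean (time coded from baseline, no group main effect); treatment × time terms apply after baseline; and the primary estimate is the day-180 difference between arms. The random effects can stay as planned. Participants with only a baseline record remain in the model, which suits the intention-to-treat aim and the expected 20% drop-out.

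Modelling day 90 and day 180 with baseline RVLT × visit as covariate is a near-equivalent alternative, but it drops those participants. Adding baseline RVLT as a covariate while baseline also stays an unconstrained response row would not achieve the gain.

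The cost is one sentence of model specification, with no new data or visits. The article reports the trial as still recruiting, so the change can be fixed before unblinding.
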